# Twelve-week randomized study to compare the effect of vildagliptin vs. glibenclamide both added-on to metformin on endothelium function in patients with type 2 diabetes and hypertension

**DOI:** 10.1186/s13098-015-0062-z

**Published:** 2015-08-26

**Keywords:** Type 2 diabetes mellitus, Hypertension, Endothelial dysfunction, Arterial stiffness, DPP-4 inhibitor

## Abstract

**Background:**

Vildagliptin, a DPP-4 inhibitor widely used for the treatment of type 2 diabetes mellitus (T2DM), shows beneficial effects on endothelial function. This study aims to evaluate the effect of vildagliptin on endothelial function and arterial stiffness in patients with T2DM and hypertension.

**Methods:**

Fifty over 35-year-old patients with T2DM and hypertension, without cardiovascular disease, will be randomly allocated to two groups: group 1 will receive vildagliptin added-on to metformin and group 2, glibenclamide added-on to metformin. Biochemical tests (glycemia, glycated hemoglobin, total cholesterol, high-density lipoprotein cholesterol, triglycerides, creatinine, alanine aminotransferase, ultrasensitive C-reactive protein, and microalbuminuria), 24-h non-invasive ambulatory blood pressure monitoring, and assessment of endothelial function and arterial stiffness will be performed in both groups before and after 12 weeks of treatment. The endothelial function will be assessed by peripheral arterial tonometry, which measures the reactive hyperemia index (vasodilation), and arterial stiffness will be evaluated by applanation tonometry. All analysis will be performed using SPSS Statistical Software. For all analysis, a 2-sided *P* < 0.05 will be considered statistically significant.

**Results:**

The study started in December 2013 and patient recruitment is programed until October 2015. The expected results are that vildagliptin will improve the endothelial function in patients with T2DM and hypertension compared to glibenclamide treatment, independently of glycemic control.

**Conclusions:**

It is expected that this DPP-4 inhibitor will improve endothelial function in patients with T2 DM.

Trial registration: Clinical Trials NCT02145611, registered on 11 Jun 2013

## Background

Cardiovascular disease (CVD) is the main cause of deaths in developing and developed countries. In Brazil, CVD accounts for more than 30 % of the overall mortality rate and is responsible for 1.2 million hospitalizations/year [1]. Hypertension (HT) and type 2 diabetes mellitus (T2DM) are among the main causes of CVD. Hypertension is the most prevalent of all CVD affecting about 30–40 % of adults (over 70 million Americans and 36 million Brazilians) [2, 3]. The prevalence of T2DM ranges from 13.5 to 15 % of the population [4, 5]. As the number of elderly population is continuously growing around the world, in the next two to three decades there will be a 200 % increase in the number of individuals with ages >65 years. The prevalence of HT and T2DM is expected to increase proportionately [6].

T2DM is associated with a twofold higher risk for CVD [7]. Endothelial dysfunction is an independent predictor for future CVD in patients with T2DM [8] and is considered an early marker of vascular complications [9]. It is involved in the atherogenesis that occurs in the early stages of coronary artery disease (CAD) [10, 11]. The mechanisms of impaired endothelial function in diabetes are: reduced bioavailability of nitric oxide (NO), diminished endothelium-dependent vasodilatation, impaired barrier function, inflammatory activation, and a pro-coagulant state [12].

Today, some groups of drugs that act on the incretin system, such as glucagon-like peptide-1 (GLP-1) analogues/agonists and dipeptidyl peptidase-4 enzyme (DPP-4) inhibitors, are used to treat T2DM and may be responsible for beneficial effects on endothelial function [13].

Incretins such as GLP-1 and glucose-dependent insulinotropic polypeptide (GIP) belong a group of gastrointestinal hormones that stimulate insulin secretion in response to the ingestion of food [13]. There is evidence of physiological signaling by GLP-1 in endothelial and vascular smooth muscle cells [14–16]. GLP-1 has a vasodilator action mediated through a specific GLP-1 receptor in the vascular endothelium and may improve endothelial function in animals and humans [14, 16]. However, cardiovascular effects may be GLP-1 receptor-independent, and mediated by the metabolites of GLP-1 [17]. One study with exenatide, a GLP-1 agonist, showed a significant increase in flow-mediated vasodilatation (FMD) [18]. Moreover, liraglutide, a GLP-1 analogue, reduced plasminogen activator inhibitor 1 (PAI-1) and asymmetric dimethylarginine (ADMA) levels, thereby improving nitric oxide availability [19]. Other researchers found increases in global myocardial blood flow following GLP-1 agonist infusions in T2DM [20], and following GLP-1 infusions in healthy humans [21].

On the other hand, DPP-4 rapidly degrades incretin hormones to inactive metabolites [13] thus DPP-4 inhibitors may improve endothelial function. Studies with sitagliptin, a DPP-4 inhibitor, demonstrated an increase of endothelial progenitor cells in T2DM by inhibiting the degradation of the chemokine stromal-derived factor 1-α [22]. According to an invasive method used to measure forearm blood flow during acetylcholine infusion in T2DM patients, vildagliptin, another DPP-4 inhibitor, improved endothelium-dependent vasodilatation [23]. In contrast, other studies did not demonstrate beneficial effects in relation to the endothelium [24, 25].

Recently, three large multicenter, randomized trials testing saxagliptin [26], alogliptin [27], and sitagliptin [28] did not find any reduction in cardiovascular events, but these drugs did not increase the risk of the primary end-point either. However, the rate of hospitalization for heart failure increased in the saxagliptin arm of the SAVOR study [26]. Thus, the researchers concluded that GLP-1 inhibitors are safe for patients with CVD.

Several methods have been used to assess impaired endothelial function including plasma concentrations of markers of endothelial activity, vessel structure related to the carotid intima media thickness and arterial stiffness, flow-mediated vasodilation (FMD) and peripheral arterial tonometry (PAT).

PAT is a simple, non-invasive, and reproducible technique used to assess endothelial function [29]. Measurements of PAT in patients with CAD have been shown to strongly correlate with the parameters of endothelial dysfunction [30–33]. The Endo-PAT is an observer-independent technique that measures volume changes in the fingertip before and after blood flow occlusion and automatically calculates the reactive hyperemia index (RHI), providing an index for endothelial function.

Arterial stiffness is another parameter used to investigate endothelial dysfunction. It is recognized as a cardiovascular risk marker [34] as impaired endothelial function is one of the mechanisms involved in increased vascular stiffness [35]. Patients with both HT and T2DM exhibit increased arterial stiffness compared to those with either T2DM or HT alone [36]. Arterial stiffness parameters predict clinical outcomes (CAD, stroke, urinary albumin excretion, progression of chronic kidney disease, survival in end-stage renal disease and general cardiovascular risk) [37–42] and have a greater importance in clinical prognoses compared to other known cardiovascular risk factors such as age, gender, smoking, and dyslipidemia [43]. The non-invasive applanation tonometry technique assesses arterial stiffness by estimating arterial compliance and central blood pressure (BP) and calculates the augmentation index (AIx) [44–46]. The AIx is a marker of wave reflection derived from aortic pressure wave analysis, with increased AIx being correlated to increased stiffness and contributing to cardiovascular risk [37, 43]. Evidence shows that the central blood pressure is more relevant to cardiovascular outcomes than the BP in the brachial artery [47–49]. More recently, a study demonstrated improvement in central BP and AIx following the use of vildagliptin in a patient with T2DM and HT [50].

Thus, using the non-invasive Endo-PAT 2000 device and radial artery applanation tonometry, the purpose of this study is to evaluate the effect of vildagliptin compared to glibenclamide both added-on to metformin on endothelial function and arterial stiffness in patients with T2DM and hypertension.

## Methods

The present trial (clinicaltrials.gov identifier: NCT02145611) will be randomized, open label, parallel assignment, controlled by drug. It was designed to assess the effect of vildagliptin (100 mg/day b.i.d.) on endothelial function in patients with T2DM and hypertension compared to glibenclamide (5–20 mg/day depending on glycemic control). The Research Ethics Committee of the institution approved the study protocol according to national and international guidelines. All patients will give their informed consent. Twenty-five individuals with T2DM and hypertension will be evaluated in the vildagliptin plus metformin group compared to 25 diabetic and hypertensive subjects in the glibenclamide plus metformin group. Figure 1 shows a flow chart of participant selection and interventions. The inclusion and exclusion criteria are presented in Table 1.

**Fig. 1 Fig1:**
[figure not shown]
Flowchart of Study

**Table 1 Tab1:** Inclusion and exclusion criteria

Inclusion criteria	Exclusion criteria
Patients aged ≥35 years	Use of NPH or regular insulin, pioglitazone, GLP-1 receptor agonist, DPP-4 inhibitor or acarbose
History of DM and mild hypertension (blood pressure <160/100 mmHg) no longer than 15 years	Intolerance to metformin
Body mass index <35 kg/m^2^	Use of three or more anti-hypertensive drugs, which characterizes resistant hypertension
Glycated hemoglobin (HbA1c) between 7.0 and 10.5 %	Smoking within the previous 6 months
	Pregnancy or breastfeeding
	Creatinine clearance <45 mL/min (MDRD)
	Serum alanine aminotransferase or aspartate aminotransferase level of more than three times the upper limit of the normal range
	Subjects with ischemic heart disease, cerebrovascular disease, other atherosclerotic disease, cancer, or heart failure in functional classes II, III and IV
	Treadmill stress test with typical chest pain or with ST segment depression ≥1 mm, or with a horizontal or descending trace on the electrocardiogram for a duration of 0.08 s after the J point
	Presence of coronary heart disease diagnosed by treadmill stress test, myocardial scintigraphy or coronary angiography
	Inability to give informed consent

## Random allocation

A computer validated software (Random allocator) will be used for random allocation. The study coordinator will organize and number the envelopes which will be allocated in order of patient enrollment. The professional responsible for the Endo-PAT procedure and applanation tonometry of radial artery will be blinded.

## Randomization and follow-up

After screening for eligibility, 50 individuals will be submitted to an evaluation of endothelial function using the Endo-PAT 2000 device and measurement of the arterial stiffness by applanation tonometry of radial artery. Subsequently, they will be randomly allocated to the two arms of the study: Group 1 will receive vildagliptin (100 mg/day b.i.d.) added-on to metformin (500–2550 mg/day according to glycemic control) and Group 2 will receive glibenclamide (5–20 mg/day according to glycemic control) added-on to metformin (500–2550 mg/day according to glycemic control). Blood samples will be collected after 12-h overnight fasting at screening visit and then after 12 weeks of treatment with vildagliptin (Group 1) or glibenclamide (Group 2). Renin-angiotensin system blockers will be prescribed to all subjects at the screening visit and all other antihypertensive drugs will be maintained. Subjects will have three return consultations. The first will be to randomize patients to Group 1 or 2 and they will be evaluated after four and 12 weeks. Compliance will be monitored by pill counts at the second and last visits. The glycemic control will be evaluated by glycated hemoglobin and fasting glucose. Adverse events will be evaluated on the basis of spontaneous reports and interviews by the investigator. Considering side effects and safety, nausea, upper abdominal pain and flatulence are expected, although uncommon, while taking vildagliptin. The most frequent side effect of glibenclamide is hypoglycemic events. Changes in blood count, renal function, and liver function are not expected with either treatment.

Table 2 shows a summary of key practical aspects of the study with all follow-up visits and requested exams.

**Table 2 Tab2:** Key practical aspects of the study with all the clinical visits and the requested exams

Visits	Screening	Visit 1	Visit 2	Visit 3
Weeks	−1	1	4	12
Informed consent	X			
Inclusion and exclusion criteria	X	X		
Medical history	X			
Medical evaluation/physical examination	X	X	X	X
Randomization		X		
Pregnancy test	X			
Creatinine	X			X
Fasting glucose	X		X	X
Ultrasensitive C-reactive protein	X			X
Total cholesterol	X			X
High-density lipoprotein cholesterol	X			X
Triglycerides	X			X
Glycated hemoglobin	X			X
Alanine aminotransferase	X			X
Microalbuminuria	X			X
Ambulatory blood pressure monitoring		X		X
Treadmill test	X			
Determination of the central aortic pressure and vascular stiffness markers		X		X
Endothelium function		X		X

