### Biochemical tests

Blood samples will be drawn after 12 h of fasting to measure total cholesterol (TC), high-density lipoprotein cholesterol (HDLc), triglycerides (TG), glycemia, serum creatinine, alanine aminotransferase, glycated hemoglobin and ultrasensitive C-reactive protein (CRP). Turbidimetry (BioSystems) will be used to measure the CRP and the possibility of patients having had acute infectious or inflammatory processes within recent weeks will be excluded. Microalbuminuria will also be evaluated. To evaluate microalbuminuria, the urinary albumin-to-creatinine ratio (UACR) will be obtained from urine samples collected in the morning. Urine creatinine will be calculated using a colorimetric method, and albuminuria will be determined using the nephelometric method. The glomerular filtration ratio (GFR) will be estimated using the Modification of Diet in Renal Disease (MDRD) formula: GFR_MDRD_ (mL/min/1.73 m^2^) = 186 (serum creatinine)^−1.154^ × (age)^−0.203^ × (0.742 if female) × (1.212 if black) [52].

Diabetic subjects will be identified by history of diabetes with dietetic treatment for diabetes or the use of hypoglycemic drugs. Subjects will be considered diabetics after two fasting glucose test results greater than 125 mg/dL according to the National Diabetes Data Group [53]. Serum cholesterol will be evaluated according to the Brazilian Guidelines for Dyslipidemias [54]. Low-density lipoprotein cholesterol (LDLc) will be calculated using the Friedewald formula for triglycerides levels below 400 mg/dL (LDLc = TC − HDLc − TG/5) [55].

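### Every subject is prescribed a renin-angiotensin blocker at screening, yet creatinine is scheduled only at screening and week 12, leaving about 13 weeks with no scheduled renal check

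*Protocol article*

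**What the plan says.** The section Randomization and follow-up sets the background antihypertensive treatment: "Renin-angiotensin system blockers will be prescribed to all subjects at the screening visit and all other antihypertensive drugs will be maintained". After the randomization visit, "they will be evaluated after four and 12 weeks". Both arms take "metformin (500–2550 mg/day according to glycemic control".

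The same section introduces the schedule: "Table 2 shows a summary of key practical aspects of the study with all follow-up visits and requested exams". The caption of Table 2 is similar: "Key practical aspects of the study with all the clinical visits and the requested exams". The rows that matter here are:

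| | Screening (week −1) | Visit 1 (week 1) | Visit 2 (week 4) | Visit 3 (week 12) |
|---|---|---|---|---|
| Inclusion and exclusion criteria | X | X | | |
| Creatinine | X | | | X |
| Microalbuminuria | X | | | X |
| Fasting glucose | X | | X | X |

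The renal exclusion criterion in Table 1 is "Creatinine clearance <45 mL/min (MDRD". Under Biochemical tests: "The glomerular filtration ratio (GFR) will be estimated using the Modification of Diet in Renal Disease (MDRD) formula".

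**The concern.** The only creatinine before week 12 is taken at the visit where the blocker is prescribed. For a subject new to the drug class, that is a pre-drug value. The next scheduled value comes at the final visit, too late to change the blocker or metformin during the study.

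Three features of the plan add to this:

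- Eligibility is checked again at Visit 1, but without a new creatinine. The 45 mL/min criterion can then be judged only on the screening result.
- Metformin is dosed by glycemic control, with no renal condition printed. At week 4 the investigator has a scheduled glucose but no scheduled creatinine.
- Adverse events are collected from spontaneous reports and interviews. These, and the physical examinations at weeks 1 and 4, would not reliably reveal a fall without symptoms.

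What is at stake is the safety of individual subjects. The blocker is given in both arms, so the treatment comparison, the power and the analysis are not at issue.

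**Working it through.** The protocol gives no figure for this gap, so there is none to reproduce. The inputs are the visit weeks in Table 2 (−1, 1, 4, 12), the MDRD exponent of −1.154 under Biochemical tests, the 45 mL/min limit in Table 1, and the study dates.

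**Gap between scheduled creatinine tests.** The week labels can be read in three ways.

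| Reading | Gap as planned | Gaps with a week-4 test |
|---|---|---|
| Printed labels | 12 − (−1) = 13 weeks | 4 − (−1) = 5, then 12 − 4 = 8 |
| No week 0 in the table | 13 − 1 = 12 weeks | 4, then 8 |
| Four and 12 weeks counted from Visit 1 at week 1 | 13 − (−1) = 14 weeks | 5 − (−1) = 6, then 13 − 5 = 8 |

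As planned, no creatinine or microalbuminuria test falls between screening and week 12. With a test at Visit 2, the longest gap is 8 weeks on all three readings.

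**Illustration at the entry limit.** In the MDRD formula, GFR is proportional to creatinine^−1.154. For a subject admitted at 45 mL/min:

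- creatinine up 10 %: 45 × 1.1^−1.154 = 40.3
- creatinine up 20 %: 45 × 1.2^−1.154 = 36.5
- creatinine up 30 %: 45 × 1.3^−1.154 = 33.2

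These rises are assumed; the document supports no particular one. The 45 mL/min limit is an entry criterion, not an on-treatment limit.

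**How many subjects a change could still reach.** The Abstract states: "The study started in December 2013 and patient recruitment is programed until October 2015". The article is dated 26 August 2015. On the printed labels Visit 2 is 5 weeks after screening, so anyone screened after 22 July 2015 had not yet reached it. Assume even recruitment of 50 subjects:

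- 1 December 2013 to 1 October 2015 (669 days, 71 of them after 22 July 2015): 50 × 71/669 = 5.3
- 31 December 2013 to 31 October 2015 (669 days, 101 of them after 22 July 2015): 50 × 101/669 = 7.5

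With a lag of 4 or 6 weeks instead of 5, the full range is 50 × 64/669 = 4.8 to 50 × 108/669 = 8.1, or about 5 to 8 subjects.

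**The case against.** **The harm is not stated in the document.** The article nowhere says that a renin-angiotensin blocker lowers renal function. This is true, and the size of any effect cannot be taken from it. However, the possibility in newly treated patients is ordinary clinical knowledge. The article's sentence expecting no change in renal function refers to the two study treatments and does not cover the blocker.

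**Table 2 is only a summary in a condensed article.** It is demonstrably incomplete: aspartate aminotransferase is an exclusion test and pill counts are planned, yet neither has a row. The text on blood sampling is not exhaustive either, since it omits the week-4 glucose. This weakens any claim that everything is listed. It does not remove the point, because creatinine has its own row, with blank cells at Visits 1 and 2, while glucose is marked at Visit 2. That is a printed choice about this test.

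**Exposure and reach are small.** Some subjects may already take the drug class, the share is unknown, and eligibility excludes the sickest patients. A subject at exactly 45 mL/min is the boundary case. Unscheduled tests remain open to the investigator, and few subjects may still be ahead of Visit 2. All of this stands and limits the importance of the finding.

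**Week 4 is not the earliest option.** A test at Visit 1 would come 2 weeks after screening and so nearer the start of the drug. But it would leave 12 − 1 = 11 weeks to the next test, against 8 from Visit 2, and Table 2 schedules no laboratory test at Visit 1.

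**Conclusion.** The concern holds as a safety-monitoring weakness in the printed schedule. A drug class is prescribed to all subjects at screening, and the next scheduled renal test comes 13 weeks later (12 to 14 depending on how the weeks are counted), when study treatment is complete. The gap follows directly from Table 2. Its clinical weight depends on two things the document does not give: how many subjects start the blocker for the first time, and how far creatinine rises in them. The estimate of 5 to 8 subjects still to reach Visit 2 rests on even recruitment. The change should be made, but no result of the trial depends on it.

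**What to change.** In Table 2, mark creatinine at Visit 2 (week 4) for all subjects still to reach that visit, and bring the text on blood sampling into line. The investigator then has a scheduled renal result on the blocker while it or metformin can still be adjusted.

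The cost is one inexpensive analyte at a visit that already has a glucose test: about 5 to 8 subjects at the publication date if recruitment is even, and never more than 50. A protocol amendment is needed because recruitment is under way. The sample size, endpoints and analysis stay as they are.

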### Anthropometric measurements

Weight and height will be measured using metric weighing scales and a measuring tape and the body mass index (BMI) will be obtained using the formula: BMI = weight (kg)/(height in meters)^2^. The waist circumference will be determined in centimeters using a measuring tape. This measurement will be carried out midway between the anterior superior iliac crest and the last rib at the end of expiration.

### Measurement of blood pressure

BP will be measured in the office using a digital sphygmomanometer according to the VI Brazilian Guidelines on Hypertension Treatment [51]. Systolic (SBP) and diastolic blood pressure (DBP) will be recorded. Hypertension will be defined as a SBP ≥ 140 mmHg and/or a DBP ≥ 90 mmHg or current use of anti-hypertensive drugs.

### Biochemical tests

Blood samples will be drawn after 12 h of fasting to measure total cholesterol (TC), high-density lipoprotein cholesterol (HDLc), triglycerides (TG), glycemia, serum creatinine, alanine aminotransferase, glycated hemoglobin and ultrasensitive C-reactive protein (CRP). Turbidimetry (BioSystems) will be used to measure the CRP and the possibility of patients having had acute infectious or inflammatory processes within recent weeks will be excluded. Microalbuminuria will also be evaluated. To evaluate microalbuminuria, the urinary albumin-to-creatinine ratio (UACR) will be obtained from urine samples collected in the morning. Urine creatinine will be calculated using a colorimetric method, and albuminuria will be determined using the nephelometric method. The glomerular filtration ratio (GFR) will be estimated using the Modification of Diet in Renal Disease (MDRD) formula: GFR_MDRD_ (mL/min/1.73 m^2^) = 186 (serum creatinine)^−1.154^ × (age)^−0.203^ × (0.742 if female) × (1.212 if black) [52].

Diabetic subjects will be identified by history of diabetes with dietetic treatment for diabetes or the use of hypoglycemic drugs. Subjects will be considered diabetics after two fasting glucose test results greater than 125 mg/dL according to the National Diabetes Data Group [53]. Serum cholesterol will be evaluated according to the Brazilian Guidelines for Dyslipidemias [54]. Low-density lipoprotein cholesterol (LDLc) will be calculated using the Friedewald formula for triglycerides levels below 400 mg/dL (LDLc = TC − HDLc − TG/5) [55].

